## Abstract

**Background:**

In the general geriatric population, programs linking geriatric evaluation with interventions are effective for improving functional status and survival of the patients. Whether or not these interventions improve health related quality of life (HRQoL) or overall survival (OS) in older patients with cancer is not yet clear. Indeed, randomized data on the effect of such interventions on survival and HRQoL are rare and conflicting. We describe the rationale and design of a phase III multicenter trial aimed at assessing the efficacy of geriatric intervention in the management of elderly patients with cancer.

**Methods/design:**

Approximately 1200 patients, 70 years and older, considered in need of a geriatric intervention based on the G8 screening tool will be randomized into two intervention arms. The ‘Usual-care’ arm involves standard oncological care based on pre-defined oncological protocols. In addition to the standard oncological care, the ‘Case-management’ arm involves a multidimensional geriatric assessment and interventions tailored for the patient. Efficacy will be assessed using a co-primary endpoint encompassing OS and HRQoL.

**Discussion:**

This trial has been designed to assess whether focused geriatric case management can either improve OS or HRQoL in elderly cancer patients considered in need of geriatric assessment.

**Trial registration:**

Clinicaltrials.gov ID: NCT02704832.

## Background

As the worldwide population ages and progress in cancer treatment increases survival, improving the management of older patients with cancer has become a major public health issue. Significant progress has been made in recent years, and geriatric assessment tools with prognostic value to identify specific problems in the elderly cancer population have been developed and validated [1–4]. However, this approach takes time and skills to administer and interpret, and only a few teams in France can perform full geriatric assessment in routine practice for all elderly cancer patients. We have developed [5] and validated the G8 screening tool [3], a short, easy-to-administer screening tool to identify patients in need of comprehensive geriatric assessment (CGA) and specialized interventions. However, the impact of further geriatric interventions on elderly cancer patient outcomes has not yet been investigated.

A number of randomized trials on geriatric interventions have shown benefit in various aspects for older cancer patients such as physical activity levels or health related quality of life (HRQoL) (Table 1). Goodwin et al. reported that nurse case management had a positive impact on the management of elderly patients with breast cancer [6]. Morey et al., in a 12-month home-based study, reported the impact of physical activity in overweight, long-term cancer survivors older than 65 years of age. They reported gains in function scores, basic lower extremity function, dietary habits and an improvement in the overall HRQoL [7]. In another study, an improvement in lean mass, muscle strength, walk time and HRQoL was observed with a resistance and aerobic exercise program for 57 prostate cancer patients with a mean age of 70 years [8]. Gains in practice of two or more goal behaviors, exercise minutes per week, total fat, saturated fat, and body mass index (BMI) were observed for 443 patients with newly diagnosed loco-regional breast or prostate cancer after a 10-month program of tailored mailed print materials [9]. Geriatric intervention reduced the pain in frail elderly patients who underwent elective surgery for a solid tumor but did not have any significant effect on delirium, complications, length of stay, care dependency and HRQoL [10].

**Table 1 Tab1:** Literature review of geriatric intervention programs

First author	Study design	N	Population	Mean age	Intervention	Primary end-point	Results
Bourdel-Marchasson [13]	Multicenter RCT*	336	Patients with solid tumor treated by chemotherapy at risk of malnutrition (17 ≤ MNA ≤ 23.5).	78.0y	3–6 months diet counselling intervention	1-year mortality	- Early dietary counselling was efficient in increasing intake but had no beneficial effect on mortality.
Hempenius [10]	Multicenter RCT	260	Frail elderly patients undergoing elective surgery for a solid tumor	≈77.5y	Geriatric liaison intervention	Postoperative delirium	- Intervention for frail elderly cancer patients receiving surgery to prevent post-operative delirium was not effective.
Demark-Wahnefried [34]	Multicenter international RCT (RENEW study)	641	Overweight long-term survivors (≥5 years) of colorectal, breast and prostate cancer	≈73y	12-month diet and exercise intervention via telephone counseling and print materials	Change in functional status (baseline/12-month and 24-month) Diet quality, BMI and physical activity	- Significant change in functional status between intervention group and control group (*p* < 0.01): amelioration of functional decline in intervention group. Significant change in diet quality, physical activity and BMI (*p* < 0.01).
Morey [7]						Change in functional status (baseline/12 m) using the Medical Outcomes Study SF36 questionnaire, health-related QoL	- Significant change in physical function (*p* = 0.03) and QoL (*p* = 0.007) between groups.
Lapid [35]	Subset geriatric analysis from stratified, two-group RCT	33	New advanced cancer diagnosis (5-year OS: 0–50 %) planned to receive radiotherapy	≈72y	4-week multidisciplinary QoL intervention	QoL measured with Spitzer uniscale and linear analogue self-assessment (LASA) at baseline and weeks 4, 8, and 27	- Significant improvement in QoL (*p* < 0.05) at baseline, maintained at 4 and 8 weeks.
Rao [14]	Subset analysis from RCT [36]	99	Frail elderly cancer patients hospitalized on a medical or surgical ward (≥2 days)	≈74y	Geriatric assessment and patient management by a geriatric attending physician and a social worker	12-month survival and health-related QoL (after randomization), ADL, physical performance, health service utilization, and costs	- No significant effect on survival or QoL parameters. Positive effects of geriatric inpatient care on mental health and bodily pain (*p* < 0.05). Days of hospitalization and cost similar.
Goodwin [6]	Multicenter RCT	335	Older women (≥65y) newly (<2 months) diagnosed with breast cancer	≈72y	12-month nurse case management	Type and use of cancer-specific therapies received in the first 6 months after diagnosis. Patient satisfaction and arm function	- More appropriate management for women receiving nurse case management (Breast-conserving surgery, adjuvant radiation, radiation therapy, axillary dissection and breast reconstruction surgery). Better arm function and higher satisfaction in intervention group.
McCorkle [15]	Single centerRCT	375	Old patients (≥60y) newly diagnosed with solid cancer	60–92	4-week home-based case management by nurse	Length of survival	- Longer survival in intervention group than in usual care group (*p* = 0.001). Survival advantage for intervention group in late stage patients.
Galvao [8]	Two-arm single center RCT	57	Prostate cancer patient without bone metastases treated by AST (≥2 months)	≈70y	12-week progressive resistance and aerobic training (2/week) by an exercise physiologist	Muscle mass, strength, physical function, QoL	- Significant change in total body lean mass, muscle strength and endurance (*p* < 0.05). Change in QoL for general health (*p* = 0.022), vitality (*p* = 0.019) and physical health composite score (*p* = 0.02).

**QoL* quality of Life, *RCT* randomized controlled trial

Geriatric intervention has also been shown to increase overall survival (OS) in the general elderly population in randomized controlled trials (RCTs) [11, 12]. However, only few RCTs have investigated the impact specifically for elderly cancer patients, with conflicting results. Bourdel-Marchasson et al. [13] found no impact on 1-year mortality after a nutritional intervention, and in a sub-analysis of a larger trial, Rao et al. [14] found no difference in 1-year survival after geriatric case-management for elderly cancer patients. An improvement in survival was reported in an RCT involving case-management in the form of a one-month nurse intervention for post-surgical elderly cancer patients, including 375 patients older than 60 years, but this benefit was restricted to the sub-population of patients with advanced disease [15].

Overall, results from various studies suggest that geriatric interventions can potentially improve OS in elderly cancer patients. Although several attempts are being made to identify more patients at risk that require geriatric interventions, any OS or HRQoL benefits following these interventions has not yet been sufficiently demonstrated.

Our objective is to conduct a two-arm phase III trial to assess the efficacy of geriatric intervention in the management of elderly patients with cancer (targeted oncology domains: breast, colorectal, lung, prostate, bladder, ovary, lymphoma). The trial will be restricted to patients with an abnormal G8 screening tool score that are considered in need of a geriatric intervention. This trial protocol was developed in collaboration with two national research platforms (Cancer and Elderly Platform and Cancer and Quality of Life Platform). We present here the key elements of the trial: objectives, study design, target population, description of the interventions, evaluation criteria and statistical methods.

## Methods/Design

### Objectives

#### Primary objective

The primary objective of the trial is to compare the efficacy of two treatment strategies “usual care” and “Case-management intervention” in elderly cancer patients considered in need of a geriatric assessment (G8 score ≤ 14). Treatment strategies are defined as follows:“Usual care”: Patients are treated according to ongoing standards in oncology.“Case-management intervention”: Patients are treated according to ongoing standards in oncology as in the “Usual care” arm. In addition, patients receive geriatric assessments and interventions coordinated by a geriatrician and a trained nurse, and tailored for the patient.

The intervention content for each arm has been precisely defined by a panel of experts in geriatric oncology. Efficacy will be assessed using a co-primary endpoint encompassing OS and three targeted HRQoL dimensions (global health status, physical functioning and emotional functioning as measured using the European Organization for Research and Treatment of Cancer, EORTC, QLQ-C 30 questionnaire [16]). Specifically, efficacy of the “Case- management intervention” will be considered superior to that of “Usual care” if, at one year, compared to usual care, improvement is observed for OS or at least one of the targeted HRQoL dimensions. We provide additional details of the primary endpoint in evaluation criteria and sample size calculation sections.

#### Secondary objectives

Secondary objectives are three-fold. First, in the population of elderly cancer patients considered in need of a geriatric assessment (G8 score ≤ 14), we will compare the two treatment strategies in terms of additional endpoints: 6-month objective response, 1- and 3-year progression-free-survival (PFS) and OS, HRQoL dimensions other than those targeted for the primary endpoint, grade 3–4 toxicities, duration and number of hospitalizations, place of residence (home versus nursing home or hospital).

Second, we will focus on the population recruited in the intervention arm. Our objective is to provide a description of geriatric parameters (evolution over one year, as well as descriptive data at baseline, 6 and 12 months): functional status, nutritional status, depression status, physical capacities, number and type of prescribed geriatric interventions.

Third, while our main focus is on elderly cancer patients considered in need of a geriatric assessment (G8 score ≤ 14), we also intend to provide a brief description of patients with a normal G8-score. Vital status, place of residence and disease progression at one year will be described.

**Fig. 1 Fig1:**
[figure not shown]
ᅟ

This study will be initially proposed to the 28 Regional Coordination Units for Geriatric Oncology accredited to the French National Cancer Institute across France, including Comprehensive Cancer Centers, teaching hospitals, public hospitals and private practices.

Data will be collected on an electronic case report form and directly input via the Internet. Data will be handled by online trial management software on the Internet; it will be transferred and monitored remotely in real-time. Similarly, randomization will proceed through internet-based software allowing rapid randomization at any time.

### Eligibility criteria

This study will include patients 70 years and older. In addition, patients must meet the following criteria: performance status 0 to 3 (WHO), candidate to 1^st^ line medical treatment (excluding best supportive care) of breast, colon, rectal, lung, prostate, bladder, or ovarian cancer and lymphomas (indolent and aggressive); excluding exclusive hormonotherapy (except prostate cancer); or, second line medical treatment (excluding Best Supportive Care) of breast, colon, rectal, prostate cancer, ovary and indolent lymphoma.

Exclusion criteria are life expectancy under 6 months, presence of any psychological, familial, sociological or geographical condition potentially hampering compliance with the study protocol and follow-up schedule, participation at the same time in another study in which investigational drugs are used, and patients who have already received two lines of treatment or for whom hormonal treatment (except for abiraterone acetate and enzalutamide in prostate cancer) or best supportive care is indicated.

### Description of the interventions

All patients included in the randomized trial will receive cancer care according to ongoing standards in oncology. The content of this intervention has been precisely defined in a *cancer care protocol* by a panel of experts in geriatric oncology, and depending on the disease and stage. For patients specifically randomized in the “Case-management intervention”, intervention will, in addition, involve multidimensional geriatric assessments and case-management geriatric interventions tailored for the patient. Similarly, this specific geriatric intervention has been precisely defined in a *geriatric care protocol* by a panel of experts in geriatric oncology. We first describe the development process for the *cancer care protocol* and the *geriatric care protocol* followed by details of the content of each protocol.

Once the protocols were drafted by the writing committee, they were sent to the peer-review committee for assessment and comments with a standardized questionnaire consisting of seven questions on the clarity, appropriateness and applicability of the proposed protocols. Members provided a formal and advisory opinion on content and form of the initial version of the guidelines. Minor modifications to the protocols were incorporated following the review. Final documents were then redistributed to the writing committees for validation. This review process was an essential quality assurance step and the final document was circulated to all participating investigators of the trial and will serve as a reference document.

#### Description of the intervention for the arm ‘Usual care’

Patients will be treated according to the *cancer care protocol*, which provides, for each cancer site, a list of treatment options as well as guidelines for dose modifications and adverse event management. The complete *cancer care protocol* is available upon request.

Patients will be followed-up by the oncologist for three years after randomization. Baseline assessment includes clinical examination, laboratory tests (hematology, biochemistry and/or creatinine clearance), disease history and treatments, tumor assessment, and HRQoL assessment (QLQ-C30 and ELD-14). Quarterly visits by the oncologist during the first year will include a clinical examination, laboratory tests, tumor assessment, and HRQoL assessment (QLQ-C30 and ELD-14 questionnaires). Patients will then be seen every semester during the second and third years during which data on disease progression, HRQoL and vital status will be collected.

#### Description of the intervention for the arm “Case-management intervention”

Patients will be treated according to the oncological standards, as defined in the *cancer care protocol*. Patients’ follow-up with their oncologist will be identical to that of patients in the ‘Usual care’ arm. In addition, intervention will also involve case-management geriatric interventions tailored for the patient. The *geriatric care protocol* provides a full description of the case-management process which includes CGAs, telephone follow-ups by the nurse and patient file reviews by the geriatrician and the nurse.

The patient will be seen by the geriatrician and the nurse for CGA at baseline (after randomization and before treatment initiation), as well as 6 and 12 months after randomization. The CGA will include the following: questionnaires completed with the nurse (Activities of Daily Living (ADL) [17], Instrumental ADL (IADL), Mini Mental State Examination (MMSE) [18], Mini Nutritional Assessment (MNA) [19], Geriatric Depression Scale (GDS-15) [20], EORTC QLQ-C 30 [16] and the Elderly Cancer Patients version (EORTC QLQ- ELD14) [21]); social evaluation including mode of living, professional help, social situation; geriatric clinical consultation including Timed Up and Go (TUG) [22], Short Performance Physical battery (SPPB [23]), weight loss, subjective health, falls in last 12 months, co-morbidities, other medical treatment, pain (numerical scale) and sleep patterns; geriatric patient management plan defined by nurse and geriatrician. The geriatric management plan establishing any necessary interventions will be defined by the nurse and the geriatrician across eleven intervention areas according to the predefined rules in the *geriatric care protocol.* Table 2 presents a summary of these interventions for the eleven intervention areas: modification of therapy, balancing chronic diseases, pain treatment, nutritional intervention, physical activity, physiotherapy, psychological support, prevention of further cognitive impairment, treatment of sleeping disorders, assistance, and home help. For illustration, with regards to nutritional intervention, weight loss over the last three and six months should be assessed and the MNA questionnaire should be completed. The patient will be considered at risk of malnutrition in case of MNA score between 17 and 23.5 and in such case, advice on increasing dietary uptake (use of food pyramid adapted for elderly patients) should be provided as presented in the *geriatric protocol*. On the other hand, in case of an MNA score below 17, weight loss greater than 5% over the last three months or 10% over the last six months, then the patient will be considered malnourished, and should be referred to a dietician.

**Table 2 Tab2:** Proposed geriatric interventions defined in protocol according to the eleven areas and screening tools used

Area	Indication	Intervention
Modification of therapy	Polypharmacy	• Re-evaluate treatment indications (with general practitioner), optimize treatment according to elderly patient protocols.
		• Use the STOPP-START* tool as a reference [37, 38].
Balancing chronic diseases	CIRS-G* Grade ≥ 3,	• Adaptation of therapy.
	arterial hypertension, diabetes, arthritis, or sensory problems	• Other non-drug interventions such as dietary advice, devices.
		• Referral to specialist doctor.
Pain treatment	Pain >1 on numeric scale	• Drug: WHO levels 1–3 antalgic treatment
		• Non-drug: physiotherapy, devices
Nutritional intervention	Malnutrition (MNA* ≤ 17)	• Referral to dietician (nutritional supplements, artificial nutrition, etc.)
	Weight loss ≥5 % over 3 m, or ≥10 % over 6 m	
	At risk of malnutrition - 17 < MNA ≤ 23.5	• Advice on increasing dietary uptake (use of food pyramid adapted for elderly patients)
Physical activity	Sedentary or at risk of falls	• Recommend daily walk, walking upstairs, carrying groceries
Physiotherapy	Difficulty with walking and balance (TUG*, and SPPB*). Fall in the last 12 m, weight loss, muscle loss	• Prescribe physiotherapy for muscular reinforcement Work on balance, and getting up from lying down position
		• Prescribe walking aids
Psychological support	GDS* ≥ 6	• Consultation with psychologist or psychiatrist
	Apparent anxiety (clinical assessment)	
	Antecedent of depression	
Prevention of further cognitive impairment	MMSE* < 24	• Behavioral monitoring during chemotherapy
		• Prevention of confusion [39]
Treatment for sleeping disorders	Positive screening score on adapted Epworth scale [40]	• Introduction, modification or discontinuation of treatment by hypnosis according to STOPP and START recommendations [37, 38]
Assistance	Social fragility identified (absence of social support)	• Ask patient directly if help is needed
		• Refer to a social worker
Home help	Difficulties performing daily tasks such as grooming, housework	• Prescribe support within the home (nursing, physiotherapy, housecleaner, etc.)

**STOPP-START* Screening Tool of Older persons’ prescriptions, *CIRS-G* Cumulative Illness Rating Scale for Geriatrics, *MNA* Mini Nutritional Assessment, *TUG* Timed Up and Go, *SPPB* Short Performance Physical battery, *GDS* Geriatric Depression Scale, *MMSE* Mini mental state examination

Telephone follow-ups by the nurse will take place on a monthly basis for the first semester, then every three months up to one year, or after any event, such as hospitalization, or change of residence to nursing home. The following information should be recorded: clinical status of the patient including factors assessed at the 1-month review, any toxicity to treatment, social assistance in place, and coordination of future consultations.

Patient file reviews will take place after telephone follow-ups and will involve the geriatrician, the nurse and the oncologist in order to review how the geriatric interventions in place are progressing, and assess the need for further interventions according to the predefined rules (Table 2).

To standardize care in the “Case-Management arm”, a two-day training for nurses will be organized. Two nurses per investigating center will participate in the training which will be mandatory before the center can accrue. During this training session, nurses will be trained to perform the telephone follow-ups with patients.

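### Grade 3–4 toxicity is compared between arms, but scheduled calls that record toxicity run in the case-management arm only, so the comparison should rest on a source common to both arms

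*Protocol article*

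**What the plan says.** The section on secondary objectives has the two strategies compared on, among other things, "grade 3–4 toxicities, duration and number of hospitalizations". The evaluation criteria name the toxicity grading scale but not the source of the events.

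Both arms share the oncologist follow-up. The usual-care section states: "Quarterly visits by the oncologist during the first year will include a clinical examination, laboratory tests, tumor assessment, and HRQoL assessment". After that, patients are seen "every semester during the second and third years during which data on disease progression, HRQoL and vital status will be collected". The cancer care protocol, which applies in both arms, supplies "a list of treatment options as well as guidelines for dose modifications and adverse event management". For the case-management arm, the article says that patients' "follow-up with their oncologist will be identical to that of patients in the" usual-care arm.

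The case-management arm then adds nurse calls, monthly in the first six months and every three months up to one year, "or after any event, such as hospitalization". The instruction for the calls reads: "The following information should be recorded: clinical status of the patient including factors assessed at the 1-month review, any toxicity to treatment". It continues: "Patient file reviews will take place after telephone follow-ups and will involve the geriatrician, the nurse and the oncologist". That arm also has comprehensive geriatric assessments (CGAs) at baseline, 6 and 12 months. Usual care has no counterpart to the calls, the CGAs or the reviews.

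**The concern.** A safety comparison is fair only if events have the same chance of being recorded in each arm. Here one arm has a scheduled enquiry about toxicity that the other lacks, and the enquiry is part of the randomised intervention. Randomisation balances patients at entry; it does not balance how hard anyone looks for events afterwards.

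The likely direction is more recorded events under case management. Lower toxicity is a plausible benefit of geriatric management, so the main danger is that a real reduction is diluted or lost. The second danger is an apparent harm where none exists.

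The file review adds a less direct route. The oncologist's visit schedule is the same in both arms, but in one arm the oncologist also takes part in reviews that follow calls about toxicity. A record kept only at the shared visits could therefore still be influenced by the calls.

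**Working it through.** The article gives no toxicity rate, capture rate or power for this endpoint, so there is no figure to reproduce. The steps below count contacts and then show how much unequal capture would matter under stated assumptions.

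**1. Scheduled contacts, from the article.**
- Year one, usual care: 4 quarterly oncologist visits.
- Year one, case management: the same 4 visits plus 6 monthly and 2 three-monthly calls, 4 + 8 = 12. This leaves out the CGAs and event-triggered calls.
- First six months: 2 visits in usual care (months 3 and 6). Case management has 2 + 5 = 7 if the month-6 CGA replaces a call, or 2 + 6 = 8 if it does not.

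These counts omit treatment visits. If each arm also has 6 to 8 of these in six months (assumption), the totals are 8 versus 13–14 up to 10 versus 15–16. The ratio falls from about 4 to between 15/10 = 1.5 and 14/8 = 1.75.

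**2. Effect of unequal capture (assumed rates).** Recorded rate = true rate × capture proportion. Take n = 600 per arm (1200 randomised 1:1) and a two-sided 5% two-proportion z-test with pooled null variance:

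P(reject) = Φ((|d| − 1.96·SE₀)/SE₁) + Φ((−|d| − 1.96·SE₀)/SE₁)

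Here d is the difference in recorded rates, SE₀ = √(2p̄(1−p̄)/n) and SE₁ = √(p₁(1−p₁)/n + p₂(1−p₂)/n).

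Example with a 40% true rate in both arms and capture of 90% (usual care) versus 95% (case management). Recorded rates are 0.36 and 0.38, d = 0.02, and SE₀ ≈ SE₁ ≈ 0.0279. The result is Φ(−1.24) + Φ(−2.68) ≈ 0.107 + 0.004 = 0.111.

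Chance of declaring a difference when none exists:

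| Capture, usual care vs case management | True rate 20% | 40% | 60% |
|---|---|---|---|
| 95% vs 97% | 5.4% | 5.9% | 7.0% |
| 90% vs 95% | 7.3% | 11.1% | 18.1% |
| 80% vs 90% | 15.2% | 31.0% | 54.7% |

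**3. Loss of a real benefit.** Suppose the true rate is 40% in usual care and 32% in case management:

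| Capture, usual care vs case management | Recorded rates | Power | Power if both arms had the usual-care capture |
|---|---|---|---|
| 95% vs 97% | 0.380 vs 0.310 | 71.8% | 79.3% |
| 90% vs 95% | 0.360 vs 0.304 | 54.0% | 76.0% |
| 80% vs 90% | 0.320 vs 0.288 | 22.6% | 68.8% |

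At high and nearly equal capture, false positives stay near nominal and the loss of power is modest. Both grow quickly as the capture gap widens. A hidden benefit is the more sensitive of the two harms.

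**The case against.** The strongest reply is that bias needs call records to feed the endpoint, and the article never says they do. The source of adverse events is a detail that an article commonly leaves to the full protocol, which may already restrict it to the shared visits. That stands: the document shows no bias. What remains is the asymmetry itself, which the article states outright and which does not depend on silence about the source.

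A reader might infer more: that toxicity goes unrecorded in usual care because the list of visit contents does not name it. The document does not support this. Both arms have clinical examination, laboratory tests and adverse event management guidelines, and the steering committee includes a pharmacist responsible for pharmacovigilance. The list is a summary; it also leaves out place of residence, another compared endpoint. The concern should not rest on that list.

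The stated purpose of the file review is to follow the geriatric interventions, not to grade toxicity, so its influence on the oncologist's record is possible but not shown. Grade 3–4 events are harder to miss than mild ones, while the calls cover toxicity of any grade and stop at one year. All capture rates above are assumed, and the article offers no support for the larger gaps.

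Hospitalisation is a thin case. An admission triggers a call, so it is already known to someone, and stays can be confirmed from records later.

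**Conclusion.** The point holds as a minor one on a secondary endpoint. Toxicity is compared between arms, and a scheduled toxicity enquiry followed by a review with the oncologist exists in one arm only. If events known only through that route are counted, recording is unequal and a true reduction could be masked.

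The size is unknown. It depends on true event rates and capture proportions that the document does not give. The illustrations run from negligible (5.4% false rejection) to serious (54.7%), and the upper end needs usual care to miss a fifth of severe events and case management a tenth. The document supports neither a claim that bias has been shown nor one that usual care lacks toxicity recording. OS is unaffected.

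**What to change.** Define the main toxicity comparison on events documented through the oncologist follow-up common to both arms. At each of those visits, ask the same structured toxicity question about the whole interval since the last visit. Add a source field to the eCRF. Report events known only from a call, CGA or file review separately, and add them back in a sensitivity analysis. For hospitalisations, confirm stays from records in the same way in both arms.

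An event documented at a shared visit should stay in the main comparison even if a call revealed it first. Dropping such events would create the opposite bias. With a 40% true rate and 80% visit capture in both arms, removing a fifth of the visit-documented events from case management alone gives 32% versus 0.8 × 32% = 25.6%, and a false benefit about 69% of the time.

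The cost is one sentence in the endpoint definition, one question set at existing visits and one eCRF field. No visits are added, and the intervention and sample size do not change. The source flag has to be collected prospectively, because it could not be rebuilt reliably at analysis.

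There are two downsides. Some true call-only events leave the main comparison, which is why the sensitivity analysis is needed. The change also reduces the influence of the calls on the oncologist's record without removing it. If that influence raised visit capture to 85% against 80% (40% true rate, 600 per arm), recorded rates of 34% and 32% would still give a false difference about 11% of the time.
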